Aim 3a: conduct an RCT wherein 10 to 12 peer coaches will be trained to deliver webMFT to 56 survivors of breast cancer, who will be randomly assigned to receive either webMFT or MVPA tracking. We will collect quantitative and qualitative data on the acceptability and feasibility of webMFT (eg, number and duration of calls delivered and barriers experienced) and suggestions for improvement from the coaches.Aim 3b: obtain data on survivor outcomes at 12 weeks from accelerometer-measured MVPA (primary outcome) and self-reported quality of life (QOL), physical functioning, mood, and fatigue to help estimate effect sizes for a larger trial to test the impact of webMFT versus MVPA tracking on survivor effectiveness outcomes. We expect that at the postintervention time point, survivors randomized to webMFT will increase MVPA; improve QOL, physical functioning and mood; and decrease fatigue significantly more than survivors randomized to MVPA tracking.Aim 3c: assess organizational-level factors (eg, the barriers and facilitators for implementation, setting and contextual factors, resources required, and alignment of webMFT with workflow and mission) using the RE-AIM and PRISM models [18] by interviewing key multilevel stakeholders at the collaborating organizations.Aim 3d: collect detailed cost, time, and resource information to conduct cost-effectiveness analyses from the perspectives of the survivors, coaches, and cancer care organizations.Aim 3e: develop a guide on how to recruit and build collaborations with other organizations that offer peer mentor programs with which webMFT can be integrated. The long-term goal of this work is to use these data to inform a robust, large-scale pragmatic trial with several cancer care organizations to deliver webMFT to survivors of breast cancer across the country.

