### Recruitment of Coaches

We will work with cancer care organizations (eg, Cancer Hope Network and Pink Lemonade Project) to recruit coaches and survivors. In total, we will recruit 10 to 12 coaches across the organizations to be trained to deliver webMFT. Each coach will be asked to work with 4 to 5 survivors over the study duration. As in our prior work [12,13], the organizations will mail or email informational letters and brochures to peer mentors, offering them the opportunity to become a coach and receive training in the delivery of webMFT.

Eligibility criteria for coaches include that they must (1) be a current peer mentor (at least 1 year) at the organization; (2) have an email address, telephone access, and access to a tablet or computer with internet to use the web platform; (3) be willing to participate in group training via videoconference; (4) be willing to have calls recorded and reviewed; (5) be willing to be supervised; (6) have a baseline level of digital literacy for this health technology (ie, sufficient internet speed and proficient in typing); and (7) currently exercise for at least 60 minutes per week.

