### Sample Size

Power calculations were based on data from our prior work with MFT [27], and data from the study by Cadmus-Bertram et al [28], who compared web-based tracking+Fitbit to pedometer alone among postmenopausal women. Comparing the effects of coach counseling [27] to web-based tracking+Fitbit [28] on changes from baseline in MVPA would yield a medium effect size, *d*=0.60. Assuming similar effect sizes and a 2-sided α=.05, we would have more than sufficient power to test intervention effects on changes in MVPA (minutes per week) at the end of intervention with 20 survivors per arm. However, given the risk of powering on pilot studies, we have conservatively inflated the sample size to 25 survivors per arm. On the basis of our prior work, we expect attrition to be ≤10% at 12 weeks, so we will recruit a total of 56 women (n=28 survivors per arm) to obtain complete data from 50 survivors.

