### Data Analyses

#### Overview

We will examine RE-AIM dimensions (Tables 1-3) to guide us in assessing the potential for larger-scale implementation of webMFT. We will conduct descriptive analyses of reach, adoption, and implementation outcomes including acceptability and feasibility of webMFT (eg, the number and mean duration of calls, barriers, and perceived feasibility of intervention delivery as judged by coaches). According to the current recommendations [46], we will consider webMFT feasible if >75% of the scheduled calls are delivered and survivor and coach and acceptability or satisfaction exceed 80% on rating scales (ratings of “moderately” to “very satisfied/acceptable”). Feedback from coaches and survivor debrief interviews will be used to revise and update webMFT for a larger-scale implementation trial.

We will assess potential between-group differences (webMFT vs MVPA tracking) in baseline variables (eg, age and medical history) using graphical methods, nonparametric and parametric tests as appropriate (eg, Wilcoxon rank-sum test for skewed data, 2-tailed *t* tests for normally distributed continuous data, and chi-squared tests for categorical data). Any variables not balanced by randomization will be controlled for as covariates in subsequent analyses, provided they are significantly associated with the outcome under consideration (at a modest *P*<.10 level).

We will assess effectiveness by examining the effects of webMFT versus MVPA tracking on the change in survivors’ MVPA in minutes per week (accelerometer data) at 12 weeks (3 months) using a mixed effects regression model, in which we will regress MVPA at 12 weeks on baseline MVPA, randomized group, wear time, and any variables not balanced by randomization. Models will include random intercepts to adjust for repeated measures within the participant over time. We will use a similar approach to estimate the effects of group on mood, QOL, physical function, and fatigue at 12 weeks. The interest is in estimating effect sizes and CIs. Analyses will be conducted on the intent-to-treat sample with all randomized participants included. Mixed effects models use a likelihood-based approach to estimation and do not require any direct imputation of missing outcomes.

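### The webMFT arm is nested in coaches, but neither the 12-week model nor the sample size allows for it; the confidence interval is too narrow for any positive coach ICC, modestly so at 2-3 women per coach

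*Protocol article*

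**What the plan says.** The Phase 2 description assigns each webMFT woman a coach, while the comparison group tracks its activity independently. Exercise Counseling has the coach make 12 weekly calls. Recruitment of Coaches plans 10 to 12 coaches across the organizations and adds: "Each coach will be asked to work with 4 to 5 survivors over the study duration".

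The Data Analyses overview regresses 12-week MVPA on baseline MVPA, randomized group, wear time and any unbalanced variables. On random effects it says: "Models will include random intercepts to adjust for repeated measures within the participant over time". A similar approach is planned for mood, quality of life, physical function and fatigue. The same section puts the interest in effect sizes and confidence intervals, and Aim 3b wants these outcome data "to help estimate effect sizes for a larger trial to test the impact of webMFT versus MVPA tracking".

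Sample Size takes a standardized effect of 0.60 and a two-sided 5% level, and considers 20 women per arm enough. It then says "we have conservatively inflated the sample size to 25 survivors per arm", giving the risk of powering on pilot studies as the reason. Neither section mentions an ICC, a design effect or a coach term.

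**The concern.** This is a partially nested design: one arm is grouped by coach and the other is not. Women who share a coach may have correlated outcomes, because coaches can differ in skill and persistence and because matching on schedule, age, treatment, race and ethnicity can bring similar women together. If so, the webMFT mean is less precise than 25 independent women would make it.

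The random effect that the plan names sits at the wrong level. With 12-week MVPA as the outcome and baseline as a covariate, each woman contributes one outcome row. A participant intercept then cannot be separated from the residual, and it carries no information about coaches.

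What is at stake is mainly the width of the confidence intervals, which the plan names as its product and which will inform a larger trial using the same kind of delivery.

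**Working it through.** **Inputs from the article.** d = 0.60, two-sided alpha 0.05, 20 then 25 completers per arm, 28 recruited per arm, attrition up to 10% (Sample Size); 10-12 coaches and 4-5 women per coach (Recruitment of Coaches).

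**Assumed.** The coach ICC, because none is given; range 0 to 0.20.

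**Step 1: the plan's own figures.** The attrition step reproduces: 50/0.9 = 55.6, so 56. Power from the noncentral t with independent women is 45.6% at 20 per arm and 54.7% at 25 per arm. The latter is the baseline for the comparison below.

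**Step 2: caseloads.** 25 women over 12 coaches is 2.1 each; 28 over 10 is 2.8 each. By contrast, 10-12 coaches with 4-5 women each makes 40-60 places for 28 webMFT women. A caseload of 4-5 occupies about 6 coaches. The two statements imply different clustering, so both were run.

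**Step 3: design effect, webMFT arm only.** DE = 1 + (Σm²/Σm − 1) × ICC, where m is a coach's caseload.
- 12 coaches (one with 3 women, eleven with 2): Σm²/Σm = 53/25 = 2.12, so DE = 1 + 1.12 × ICC.
- 10 coaches (five with 3, five with 2): 65/25 = 2.60, so DE = 1 + 1.60 × ICC.
- 6 coaches (one with 5, five with 4): 105/25 = 4.20, so DE = 1 + 3.20 × ICC.

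**Step 4: consequences.** Effective webMFT n = 25/DE. The correct standard error is √((DE + 1)/2) times the unadjusted one, so the unadjusted interval is too narrow by 1 − 1/√((DE + 1)/2). Power uses the noncentral t (48 df) with variance DE/25 + 1/25. Type I error is that of an unadjusted t test, simulated 40,000 times per row with total variance 1 in both arms.

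| Coaches | ICC | DE | Effective n | Interval too narrow by | Power | Type I error |
|---|---|---|---|---|---|---|
| any | 0 | 1.00 | 25 | 0% | 54.7% | 5.0% |
| 12 | 0.05 | 1.06 | 23.7 | 1.4% | 53.6% | 5.5% |
| 12 | 0.10 | 1.11 | 22.5 | 2.7% | 52.5% | 5.5% |
| 10 | 0.05 | 1.08 | 23.1 | 1.9% | 53.1% | 5.6% |
| 10 | 0.10 | 1.16 | 21.6 | 3.8% | 51.6% | 6.0% |
| 6 | 0.05 | 1.16 | 21.6 | 3.8% | 51.6% | 5.7% |
| 6 | 0.10 | 1.32 | 18.9 | 7.2% | 48.8% | 7.0% |
| 6 | 0.20 | 1.64 | 15.2 | 13.0% | 44.0% | 8.9% |

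Simulation noise is about 0.1 percentage point. At ICC 0.20 with 10-12 coaches, DE is 1.22-1.32 and the interval is 5-7% too narrow.

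**Step 5: what the coach variance estimate can deliver.** With 25 women over 10 coaches, a one-way analysis of variance puts the coach variance at or below zero in about 44% of trials when the true ICC is 0.05, and in about 36% when it is 0.10. An observed ICC of 0.10 would carry a 95% interval of roughly −0.3 to 0.6.

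**The case against.** **The ICC may be close to zero.** Delivery is standardized: set counseling questions, common training, supervision every other week and an audit of 10% of calls. A reader might infer that the interval is certainly too narrow. The article does not support that, because it gives no ICC. Only the conditional statement holds. Standardized delivery makes a small ICC plausible but does not make it zero.

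**The larger figures need about 6 coaches.** With the stated 10-12 coaches and even caseloads, the effect is a few percent. This stands, and the 2-3 caseload should lead. The 4-5 caseload is nevertheless the plan's own figure, and because matching requires overlapping schedules, caseloads may be uneven, which raises the design effect.

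**Type I error is the weaker argument.** If coaching changed nobody's activity, differences between coaches could not create clustering. Inflation under the null needs either coach effects that average to zero or non-random sorting through matching. This largely stands; interval coverage is the firmer ground.

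**A coach term could appear in a fuller analysis plan.** Possibly. But the article does specify the model's fixed terms and the level of its random effect, and nothing elsewhere in it allows for coach.

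**The pilot cannot supply an ICC for sizing the larger trial.** Correct, as Step 5 shows. A reader might infer that a key sizing quantity is being withheld; at this size the estimate would be too imprecise to serve alone.

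**Clustering is not the main sizing problem.** Also correct. Power at d = 0.60 is about 46-55% before any design effect, and clustering removes a few more points.

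**Conclusion.** The point holds in conditional form. The planned analysis and sizing make no allowance for coach, although only the webMFT arm is grouped by coach and the stated random intercept cannot pick this up. For any positive coach ICC, the effective webMFT sample is below 25 and the interval too narrow.

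At 2-3 women per coach and an assumed ICC of 0.05-0.10, the shortfall is modest: about 1-4% in interval width, with type I error of about 5-6%. At 4-5 women per coach and ICC 0.10, it is about 7% in width, with type I error of about 7%. These figures rest on the assumed ICC, near-even caseloads and the planned 25 completers per arm. The Results section reports 61 women enrolled against 56 planned, so the actual arms may be somewhat larger.

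The improvement is worth making because intervals are the stated product and the change is cheap. It is not grounds for recruiting more women.

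**What to change.** **Data Analyses.** Fit the 12-week models for MVPA, mood, quality of life, physical function and fatigue as partially nested models: a random coach effect in the webMFT arm only, each tracking woman as her own unit, and Satterthwaite or Kenward-Roger degrees of freedom. At the least, prespecify this as a sensitivity analysis beside the ANCOVA. If the coach variance is estimated at zero, the model reduces to that ANCOVA. Report the coach variance with its confidence interval as descriptive only.

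**Sample Size.** State that 25 per arm assumes no coach clustering. Give the effective webMFT n over an assumed ICC range for both caseloads; for ICC 0.05-0.10 this is about 21.6-23.7 with 10-12 coaches and about 18.9-21.6 with 6.

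**Recruitment of Coaches.** Reconcile 10-12 coaches at 4-5 women each (40-60 places) with 28 webMFT women.

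**Cost.** One model term and a few sentences. The platform makes the matches and tracks the calls, so coach identity should already be available. The downside is a slightly wider interval and a coach variance that will often be estimated at zero.

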#### Effectiveness

Intervention effectiveness, operationalized as changes in survivors’ MVPA (primary outcome), will be assessed at the postintervention time point (3 months; Table 1).

Postintervention assessments will follow the same procedures as at baseline: the questionnaires will be completed via REDCap and staff members conducting assessments will be blinded to the survivors’ group assignments. Staff members will mail the accelerometer to the patients. When the units are returned by mail and web-based questionnaires completed, survivors will receive a US $25 gift card (US $25×2 assessments=US $50). The assessments are described in Tables 1 and 3 and include the following:

Accelerometer: we will use the Actigraph accelerometer (GT3X) as a device-based and gold standard measure of MVPA. Survivors will be asked to wear the unit around their waist during all waking hours over a 7-day period. The Actigraph will be worn at baseline and the postintervention time point. The Freedson cut points [30] will be used to score the data; data will be collected in 10-second epochs. A valid accelerometer day is defined as >10 hours per day; participants are required to have 4 valid days of wear.QOL, physical functioning, fatigue and mood will be assessed using validated and standardized questionnaires that have been used by patients with breast cancer. Survivors will be asked to complete the following standardized questionnaires via REDCap: Functional Assessment of Cancer Therapy Scale-Breast [31], a 36-item Short Form Health Survey that includes a Physical Functioning subscale [32], Functional Assessment of Cancer Therapy Scale-Fatigue [33], and the Profile of Mood States [34]. In addition, the following questionnaires will be used to assess the constructs relevant to the TTM and SCT: Stage of Readiness for Exercise [35] and Exercise Self-Efficacy [36].Program value will be assessed during semistructured interviews at the study end with survivors to understand how webMFT impacted the health and well-being of the survivors (Table 3).

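### The primary model adds a participant random intercept to a single 12-week outcome, so it amounts to a complete-case ANCOVA and lacks the intent-to-treat and missing-data properties claimed for it

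*Protocol article*

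**What the plan says.** The model is given in the Protocol article under Data Analyses, Overview. The target is the "change in survivors’ MVPA in minutes per week (accelerometer data) at 12 weeks (3 months) using a mixed effects regression model", and the specification is that "we will regress MVPA at 12 weeks on baseline MVPA, randomized group, wear time, and any variables not balanced by randomization". Three statements follow about this model:

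- On its structure: "Models will include random intercepts to adjust for repeated measures within the participant over time".
- On the analysis set: "Analyses will be conducted on the intent-to-treat sample with all randomized participants included".
- On missing data: "Mixed effects models use a likelihood-based approach to estimation and do not require any direct imputation of missing outcomes".

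The secondary outcomes inherit all of this: "We will use a similar approach to estimate the effects of group on mood, QOL, physical function, and fatigue at 12 weeks".

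The assessment schedule is in Measures, Effectiveness: "The Actigraph will be worn at baseline and the postintervention time point". Table 1 agrees, listing baseline and 12 weeks only. The Effectiveness section also requires 4 valid days of accelerometer wear. Sample Size expects attrition of at most 10% and recruits 56 women so that 50 have complete data. Results reports 61 enrolled as of September 2023.

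**The concern.** A participant random intercept needs at least two outcome values for at least some participants. Here one of the two MVPA values is used as a covariate, which leaves one value per woman as outcome. The outcome is a weekly total, so there are no daily rows either, and no other grouping level (coach, for example) is named for the intercept.

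The missing-data sentence depends on the same structure. Likelihood estimation in a mixed model uses a partly observed participant through the outcome rows that she does have. With a single outcome row, a woman who lacks it has no other row to contribute.

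At stake is what the primary result may be called. A completer analysis would be reported as intent-to-treat with all randomized women included, and the missing-data question would look settled when it has not been addressed. Aim 3b wants the effect size to plan a larger trial, so readers of that estimate should know whom it is based on.

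**Working it through.** **1. The plan's own figure.** Inputs from Sample Size: 50 complete, attrition 10%. 50 / (1 − 0.10) = 55.6, rounded up to 56; per arm 25 / 0.90 = 27.8, rounded up to 28. This reproduces the stated 56 (28 per arm).

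**2. Outcome rows per woman.** There are two assessments (Effectiveness; Table 1), and one is on the right-hand side: 2 − 1 = 1 row.

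**3. Variance components.** Write the stated model as Yᵢ = xᵢ′β + bᵢ + eᵢ, with xᵢ holding baseline MVPA, group, wear time and any other covariates, Var(bᵢ) = σ_b² and Var(eᵢ) = σ_e². With one row per woman,

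Var(Y) = (σ_b² + σ_e²) × I.

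The likelihood depends only on the sum σ_b² + σ_e², so the split is not identified. Because the variance matrix is proportional to the identity, generalized least squares gives the ordinary least-squares β: the group effect is identified and equals ANCOVA.

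**4. Numerical illustration.** One simulated data set; all settings are assumptions: 56 women, 28 per arm; baseline mean 60, SD 35; 12-week value = 20 + 0.5 × baseline + 24 × group + error of SD 35; wear time unrelated to outcome; 6 women without a 12-week value, chosen at random.

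| Check | Result |
|---|---|
| Log-likelihood at intercept shares 0, 25, 50, 75 and 99% | −240.499643 each time |
| Group estimate at each share | 28.08 |
| Mixed-model fit | 28.08 (SE 8.78); variances 479.3 and 479.3; warning that the Hessian is not positive definite |
| ANCOVA on the 50 completers | 28.08 (SE 8.82) |

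The equal split is arbitrary. The treatment estimate is unaffected.

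**5. Who contributes.** For a woman with no 12-week value, the stated model's likelihood term is the density integrated over all possible outcomes, which is 1, so her log-likelihood contribution is 0. At planned attrition, 56 − 50 = 6 women drop out of the fit (6 / 56 = 10.7%). With 61 enrolled, 61 × 0.10 = 6.1, so about 6 drop out and about 55 remain. Since attrition is given as at most 10%, these are ceilings for attrition. Women who return the device with fewer than 4 valid days may add to them; the article gives no figure for that.

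**6. Using both time points as outcomes.** In the same simulated data, a random-intercept model with both values as outcome rows and a common baseline mean used all 56 women (56 + 50 = 106 rows) and separated the two variances (482 and 567). That restores the meaning of the random intercept but recovers little about treatment. With an unstructured 2 × 2 covariance and no further covariates,

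E(Y₁ | Y₀, g) = μ₁ + δg + β(Y₀ − μ₀).

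The coefficient of g is δ, the group-by-time effect. The likelihood factors into a baseline part and a 12-week-given-baseline part. Baseline-only women enter just the first, which carries no information on δ, so the maximum-likelihood estimate of δ is the complete-case ANCOVA estimate. A simulation agreed (200 data sets; assumed n = 56, correlation 0.5, effect 0.60 SD, about 10% missing depending on baseline): the two estimates matched to within 5 × 10⁻⁷ in every data set (mean 0.597, SD 0.253 for both).

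**7. When the estimate could move.** Complete-case ANCOVA is valid if missingness depends only on the model covariates. In an illustrative simulation where dropout followed activity during the study, it gave 0.66 against 0.61 with full data. That dropout mechanism is assumed, so this shows only that a difference can arise and is not a size for this trial.

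**The case against.** The strongest reply is that nothing goes wrong with the number reported. The article says that interest lies in effect sizes and confidence intervals; variance components are no target. The group estimate equals ANCOVA, complete-case ANCOVA is a respectable analysis under a stated condition, and Sample Size openly plans on 50 complete cases. Imputation details and sensitivity analyses commonly belong in a statistical analysis plan, so their absence from an article is no fault.

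Most of this stands, and it limits the point. A reader might infer that the primary analysis fails or that the treatment effect is not identifiable. The model does not support that: only the split between the two variances is lost.

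A reader might also picture an analyst stacking baseline and 12-week rows to satisfy the random-intercept sentence, while keeping baseline as a covariate and a single group term. That would average a zero effect at baseline with the true effect at 12 weeks: (0 + 0.60) / 2 = 0.30. But the article regresses the 12-week value and nowhere proposes such a model, so the halving is not a fault of this plan.

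What the reply does not meet is the contradiction in the text. The point does not rest on missing detail. The article states a model, a reason for its random intercept, an analysis set and a missing-data argument, and the last three do not follow from the first.

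**Conclusion.** The concern holds as an inconsistency of specification and description in the primary analysis. As written, the model is an ANCOVA on women with a valid 12-week value, with a redundant random intercept. It omits up to about 6 of 56 women at the planned attrition, or about 6 of the 61 enrolled, so the all-randomized claim and the no-imputation argument are unsupported.

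The algebra in steps 3 and 5 needs only the stated model and the two-visit schedule. The counts rest on the plan's own 10% ceiling. No bias is demonstrated for this trial: that would need missingness to depend on something outside the model, which the documents neither show nor exclude. Since the treatment effect remains estimable and the repair is cheap, I rate this should-fix rather than must-fix.

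**What to change.** Reconcile the sentences in Data Analyses, Overview, by choosing one of two routes.

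- **Preferred.** State a plain ANCOVA of 12-week MVPA on baseline MVPA and group, with the other covariates kept as planned and no participant random intercept. Multiply impute missing 12-week MVPA within arm, using baseline MVPA, the two stratification factors (age and chemotherapy) and the weekly Fitbit minutes already collected in both arms. If the wear-time covariate is the 12-week one, it is missing for the same women and must be imputed too. Delete the random-intercept and no-imputation sentences. Fitbit minutes help only for weeks in which a woman wore and synced the device, so the gain should not be oversold.
- **Alternative.** Model baseline and 12-week MVPA both as outcomes, with a common baseline mean, a group-by-time effect and an unstructured covariance, and drop baseline as a covariate. The likelihood sentence may then stay. Without further covariates the treatment estimate is the same as in complete-case ANCOVA, so this route makes the description true but recovers no information.

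Apply the same choice to mood, QOL, physical function and fatigue. The cost is revised wording and a little more analysis work; no new data and no change to the design are needed.
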